### Study population

Women with a family history of breast cancer who are first-time attendees applying for breast cancer counselling are invited to participate in the study. A family history of breast cancer is defined as having or having had at least one first-degree- and/or paternal second-degree family member with breast cancer. Women are considered ineligible if they are under 18 years of age, have evident psychiatric illness or terminal disease, and are unable to read and write Dutch. Women with a personal history of breast or ovarian cancer are also excluded, because of the complexities in risk counselling of women with a previous history of cancer. Participants are allocated into an intervention or control group (for randomisation procedure, see below). Stratification to first-degree family members is applied to ensure that all family members receive the same condition.

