### Randomisation

Randomisation takes place at 'condition round' level. The inclusion period is divided into condition rounds using a Latin Square design. Every round takes 5 months and switches when a total of n = 75 is reached. The ranking order of conditions (1–5) is varied to correct for learning effect by the risk counsellors. Each condition is given according to the design shown in Table 2. The control group (condition 6) is constructed in addition to each condition round.

**Table 2 T2:** Latin square design of condition rounds over time at the three clinical genetic centres

	**Conditions**^a^				
	months 1–5	months 6–10	months 11–15	months 16–20	months 21–25

Centre A	1	2	3	4	5
Centre B	2	3	4	5	1
Centre C	5	1	2	3	4

^a^. 1) lifetime risk in numerical format (natural frequencies); 2) lifetime risk in both numerical format and graphical format (population figures); 3) lifetime risk and age-related risk in numerical format; 4) lifetime risk and age-related risk in both numerical format and graphical format; 5) lifetime risk in percentages. Condition 6 (control group) is constructed in addition to each condition round.

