### Procedure

Women applying for genetic breast cancer counselling are invited to participate by means of an information letter send to their home address. All participants provide written informed consent. In the intervention group, participants receive a self-administered questionnaire at four points in time (T0, T1, T2, T3), the control group receives this at three points in time (T0, T1C, T2C) (see Figure 1):

- T0 (baseline): The women will receive the first questionnaire at home before their first appointment with the genetic counsellor.

- T1 (after standard counselling session): A second questionnaire will be given after the standard genetic counselling session with the genetic counsellor and prior to the intervention (additional counselling with the risk counsellor).

- T2/T1C (2 weeks follow-up): A third questionnaire will be sent to the woman's home address at 2 weeks after the intervention, or a comparable point in time (control group).

- T3/T2C (6 months follow-up): The final questionnaire will be sent to the woman's home address.

A maximum of two reminders is sent to participants not returning their questionnaires. The three risk counsellors (one for each clinical genetics centre) who provide the intervention, have been specifically trained for this study. The intervention lasts for approximately 30 minutes. The risk counsellor is informed about the content of the previous standard counselling session by means of a "checklist after standard counselling", which the genetic counsellor fills in immediately after each session. This checklist includes information about the participant's risks e.g. individual estimated risk of getting breast cancer, also describing the risks formats that were used during counselling. When risks are not yet known, because, for instance, medical records need to be checked, intervention takes place after a second visit. Thus, enforcement of an intervention implies that in the genetic counselling session with the genetic counsellor at least the woman's breast cancer risk group (e.g. low, moderate, high) was communicated.

After the intervention, all participants receive a BRISC brochure in which risks are presented corresponding to the format of the intervention given.

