### Statistical analyses

Analyses will be performed to estimate the effect of the different interventions (formats) by comparing pre-test- (T0/T1) with post-test- (T2/T1C) outcome measures between the five different intervention groups and the control group, using multivariate analyses. At baseline (T0) and at T1 similar variables will be measured in order to be able to assess the effect of the regular counselling session with the genetic counsellor. Personal variables will be included as covariates. Repeated measures in MANOVA will be used to analyse changes over time and long-term effects (T3/T2C).

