Two control conditions are introduced in the BRISC study: condition 5 in which the risk information is communicated in percentages as is commonly done in usual care, and a second control condition (condition 6) in which no intervention is given. With these two control conditions, it is possible to distinguish between the effect of repetition and the effect of giving the risks in a structured way on the one hand, and between the effects of giving the risks in a structured way in different formats on the other.

Because the genetic counsellor involved has no role in the inclusion of participants, selection bias is restricted, other than from self-selection. Cluster-randomisation is applied as it is too complex to randomise at the level of counsellees because in that case a risk counsellor is asked to give different risk formats of genetic risks to different counselees on the same day. An exception is made for participants who are close family members.

The risk counsellors who give the intervention are not involved in usual care. This will overcome concerns of contamination bias. All risk counsellors are women, eliminating bias due to gender differences. The Latin Square design and the control group, which is constructed in addition to all condition rounds, both serve to eliminate bias due to time. To achieve uniform risk communication in the genetic counselling sessions, several precautions have been taken (e.g. striving for a standard counselling procedure, "counselling checklist", "checklist after standard counselling"), minimising confounding.

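### Conditions 1–5 are allocated by centre-round, but the stated analysis treats women as independent and names no round or centre-round term

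*Protocol article*

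**What the plan says.** On allocation, the Randomisation section says "Randomisation takes place at 'condition round' level". The Discussion gives the reason: "Cluster-randomisation is applied as it is too complex to randomise at the level of counsellees". Table 2 sets out three centres by five rounds, with one format per centre in each round. On round size: "Every round takes 5 months and switches when a total of n = 75 is reached". Usual care is handled differently: "The control group (condition 6) is constructed in addition to each condition round". Close relatives are kept together (Study population): "Stratification to first-degree family members is applied to ensure that all family members receive the same condition".

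On analysis, the Statistical analyses section compares pre-test with post-test measures between the five intervention groups and the control group by multivariate analyses, with personal variables as covariates. For later follow-up: "Repeated measures in MANOVA will be used to analyse changes over time and long-term effects (T3/T2C". It states no term for centre, round, centre-round or family. The Sample size and power section states no ICC or design effect.

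**The concern.** Repeated-measures MANOVA models the correlation between one woman's own questionnaires. It assumes that different women are independent. All women seen at one centre in one round receive the same format, so anything they share (case mix in those months, a change in local counselling, how the format was being delivered then) cannot be told apart from the format unless the model says so.

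The contrasts most exposed are those among conditions 1–5, which answer research questions 1–3. The Discussion says that a format found most effective could be built into standard counselling, so a false positive could change practice.

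**Working it through.** **1. The plan's own figures.** 6 × 60 = 360 and 360 / 0.80 = 450, as stated. The 60 per condition cannot be re-derived, because no SD or base rate is given. For two independent groups at 80% power and two-sided 5%, 60 per group corresponds to a difference of 0.51 SD with no allowance for clustering.

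**2. Clusters.** 3 centres × 5 rounds = 15 cells, or 3 per condition. Reading the 75 as the conditions 1–5 total for a round, 5 × 75 + 75 controls = 450, and 75 / 3 = 25 women per cell if centres recruit equally. After 20% drop-out, m = 20 analysed women per cell.

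**3. Error rate by formula.** The design effect is DE = 1 + (m − 1) × ICC. The true two-sided error of the unadjusted test is 2 × [1 − Φ(1.96 / √DE)].

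| Assumed ICC | DE | True error |
|---|---|---|
| 0 | 1.00 | 5.0% |
| 0.01 | 1.19 | 7.2% |
| 0.02 | 1.38 | 9.5% |
| 0.05 | 1.95 | 16.1% |

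**4. Error rate by simulation.** Table 2 layout, 20 women per cell plus 4 controls per cell, no true effect, cells ignored in the analysis. Rounded results:

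| Assumed ICC | Pair within 1–5 | Five-condition F test | Condition 1 vs 6 |
|---|---|---|---|
| 0 | 5% | 5% | 5% |
| 0.01 | 7% | 9% | 6% |
| 0.02 | 10% | 15% | 6–7% |
| 0.05 | 16% | 30% | 9–11% |

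The last column is smaller because condition 6 is spread over all cells.

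**5. Which component matters.** A pure centre effect (variance share 0.05) gives 4.4–5.2%, that is, no inflation, because every centre delivers every condition. Fixed centre and round terms alone do not cure centre-round correlation: at ICC 0.05 a pairwise test still rejects about 16–17% of the time.

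**6. Balance over time.** Rounds in which each condition runs (centres A, B, C in Table 2):

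- Condition 1: 1, 5, 2; mean 2.67
- Condition 2: 2, 1, 3; mean 2.00
- Condition 3: 3, 2, 4; mean 3.00
- Condition 4: 4, 3, 5; mean 4.00
- Condition 5: 5, 4, 1; mean 3.33

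With a linear drift of d per round and no round term, the biases are:

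- Condition 4 vs 2: 4.00 − 2.00 = 2d.
- Age-related effect: (3.00 + 4.00)/2 − (2.67 + 2.00)/2 = 1.17d.
- Graphical effect: (2.00 + 4.00)/2 − (2.67 + 3.00)/2 = 0.17d.
- Interaction: (4.00 − 3.00) − (2.00 − 2.67) = 1.67d.

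A random round effect shared by all centres, with variance share 0.02, gives about 6% for a pair and 8–9% for the overall test. A fixed round term brings both back to 5%.

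**7. Power of an analysis that respects the cells.** For conditions 1–5, the cell-mean analysis with condition, centre and round has 14 − 4 − 2 − 4 = 4 residual degrees of freedom (critical t = 2.776). A pairwise contrast has variance q × [ICC + (1 − ICC)/20], with q = 0.764 or 0.873 depending on the pair. For 0.51 SD at ICC 0, the non-centrality is 0.51 / √(0.764 × 0.05) = 2.6 or 0.51 / √(0.873 × 0.05) = 2.4, giving power of 51% or 46%. At ICC 0.02 it is 36–40%, and at ICC 0.05 it is 27–30%.

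**The case against.** The strongest reply is that this is a four-sentence summary in a journal article: stating no round term is not a commitment to leave one out, and the fuller plan is not shown. That limits the wording to what is stated. It does not remove the point, because the article names a method, and that method's independence assumption conflicts with the allocation the article itself calls cluster randomisation. The MANOVA sentence also covers only change over time and long-term effects. The main pre–post comparison is described more loosely as multivariate analyses, which could accommodate extra terms, but only personal variables are named.

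The design does offer protection. Varied condition order and concurrent controls address learning and time, and the Latin square balances stable centre differences. But with three rows of five rounds it balances time only in part (step 6).

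A reader might infer more than the documents support:

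- **That the error rate definitely exceeds 5%.** This needs positive correlation within centre-rounds. No ICC is given, and comparing change from T0/T1 with covariates may lower it.
- **That having one risk counsellor per centre ("The three risk counsellors (one for each clinical genetics centre") drives the problem.** Stable counsellor differences coincide with centre and are balanced.
- **That the family rule matters as much.** With an assumed 1.05–1.2 participants per family and a family ICC of 0.1–0.5, the design effect is only about 1.005–1.10.
- **That women with a missing questionnaire will be discarded.** The article does not say how missing data are handled, so this is no part of the point.

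**Conclusion.** The point holds in this form: the stated analysis does not match the stated allocation for conditions 1–5. Its size is conditional. At assumed centre-round ICCs of 0.01, 0.02 and 0.05, with about 20 analysed women per cell, a nominal 5% test has a true error of about 7, 10 and 16% for a pair among conditions 1–5 and 9, 15 and 30% across all five. For a format against usual care it is about 6, 6–7 and 9–11%. At ICC 0 there is no inflation.

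Separately, without a round term, calendar drift biases some format contrasts. Condition 4 against 2, the interaction and the age-related effect are the most exposed; the graphical main effect is hardly affected. The drift itself is unknown, so the bias can be stated only per unit of drift.

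**What to change.** In Statistical analyses, replace the MANOVA with a linear mixed model for the post-intervention measurements:

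- fixed effects for condition, centre, round and the baseline value;
- a random effect for centre-round, which fixed centre and round terms cannot replace;
- a random effect for woman, for the repeated measurements;
- small-sample degrees of freedom (for example Kenward–Roger).

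Report a cell-mean analysis of conditions 1–5 (4 residual degrees of freedom) as a check. Treat family clustering as a sensitivity analysis, since a family effect may be barely estimable if most families contribute one woman.

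No new data are needed: centre, round and family are known from the allocation. The cost is precision. Intervals widen, and in the cell-mean analysis power for 0.51 SD between two of conditions 1–5 is about 46–51% at ICC 0 and 27–30% at ICC 0.05, against the stated 0.80. Sample size and power should therefore say that its 0.80 does not account for clustering.

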## Discussion

Understanding risks is considered to be crucial for informed decision-making. However, inaccurate risk perception is a common finding in women attending genetic counselling regarding breast cancer. Although the literature provides recommendations for the use of frequencies, graphical displays and short-term risks such as age-related risks (i.e. risks for the next ten years) in risk communication, these recommendations are based primarily on research using hypothetical scenarios. In addition, the recommended approaches are not generally used in standard care. The BRISC study is designed to fill the gaps with an evaluation of the effects of different formats of communicating risks to counsellees facing real decisions in a clinical setting. Results will be used to improve risk communication in order to stimulate informed decision-making among women with a family history of breast cancer.

The BRISC study is a field study; in other words, a clinical trial which offers a unique opportunity to evaluate effects of different formats of communicating risks to counsellees facing decisions such as informing relatives who may also be at risk, whether and when to start mammography screening, and, assuming eligibility, whether to test for mutations in *BRCA1/2*.

Quantitative outcome measures are collected using questionnaires at four points in time. The follow-up questionnaire is sent 6 months after the intervention, thereby enabling medium-term effects to be detected. With this comprehensive collected data, it will be possible to clarify the various effects of different formats on four dimensions evaluating the effectiveness of the risk communication process. It is not inconceivable to expect that some formats have positive effects on one of the dimensions and negative effects on another dimension. Additionally, the outcomes of this project will give a better understanding of who, for example, as a function of cognitive capacity, might or might not benefit from different formats.

Two control conditions are introduced in the BRISC study: condition 5 in which the risk information is communicated in percentages as is commonly done in usual care, and a second control condition (condition 6) in which no intervention is given. With these two control conditions, it is possible to distinguish between the effect of repetition and the effect of giving the risks in a structured way on the one hand, and between the effects of giving the risks in a structured way in different formats on the other.

Because the genetic counsellor involved has no role in the inclusion of participants, selection bias is restricted, other than from self-selection. Cluster-randomisation is applied as it is too complex to randomise at the level of counsellees because in that case a risk counsellor is asked to give different risk formats of genetic risks to different counselees on the same day. An exception is made for participants who are close family members.

The risk counsellors who give the intervention are not involved in usual care. This will overcome concerns of contamination bias. All risk counsellors are women, eliminating bias due to gender differences. The Latin Square design and the control group, which is constructed in addition to all condition rounds, both serve to eliminate bias due to time. To achieve uniform risk communication in the genetic counselling sessions, several precautions have been taken (e.g. striving for a standard counselling procedure, "counselling checklist", "checklist after standard counselling"), minimising confounding.

Some limitations of the BRISC study need to be addressed. This study aims at improving women's understanding of the risks, and we acknowledge that there are factors other than risk that can influence the decision-making process. In addition, although several precautions have been taken to achieve an optimal standardisation in counselling and procedures, interactive features must be acknowledged. Another limitation of this study is that it is not possible to blind the genetic counsellors completely because of the nature of the intervention. This applies to the intervention allocation and to the age-related formats due to anticipation of questions by the counsellee. Participants are informed that the BRISC study concerned different kinds of risk counselling and are blinded. Furthermore, although we would have preferred to test an integrated intervention in standard counselling sessions, it is not considered feasible, either ethically or practically, to have the intervention done in a structured way by the genetic counsellors themselves. If one of the formats proves to be most effective, this format could be integrated into the standard counselling session. Since members of the research team provided the additional consultations (interventions), implementation of a format in daily practice will need to receive further attention.

Finally, results may be extended to women with a personal history of cancer, other cancers, and also other diseases and settings, but further study would be required. Imprudent generalization should be avoided, although the BRISC study may provide an indication for risk communication in healthcare in general and cancer genetic counselling in particular.

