**Figure 1 F1:**
[figure not shown]
Time planning of the intervention and questionnaires in the intervention group (conditions 1–5) and control group (condition 6).

During the additional consultation, risks are communicated in one of five ways (conditions), namely:

1) lifetime breast cancer risk in numerical format (in natural frequencies, i.e. X out of 100),

2) lifetime breast cancer risk in both numerical format and graphical format (i.e. population figures in 10 rows of 10),

3) lifetime breast cancer risk and age-related breast cancer risk in numerical format,

4) lifetime breast cancer risk and age-related breast cancer risk in both numerical format and graphical format, and

5) lifetime breast cancer risk in percentages.

Since the information given during the intervention not only differs from usual care regarding the format of the risks but also to the extent to which the information is structured, two control conditions are included. Condition 5, in which the risk is communicated in percentages as in the standard genetic counselling session (usual care), controls for the effect of giving risk information also in a structured way, enabling us to compare the effects of different risk formats. Condition 6, in which no intervention is given (usual care, henceforth defined as the control group) is used to control for the effect of repetition of the risk information (as compared to condition 5), and will control for Hawthorne effects [38].

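### Conditions 5 and 6 cannot separate the effect of repetition from the effect of structured presentation; their contrast estimates the additional consultation as a whole

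*Protocol article*

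**What the plan says.** The Intervention section gives the two control conditions separate roles. Condition 5, the additional consultation with risks in percentages, "controls for the effect of giving risk information also in a structured way". Condition 6, usual care without the additional consultation, "is used to control for the effect of repetition of the risk information (as compared to condition 5), and will control for Hawthorne effects". The Discussion draws the conclusion that with both conditions "it is possible to distinguish between the effect of repetition and the effect of giving the risks in a structured way", and adds that the formats can also be told apart from one another.

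The Procedure section describes what the groups receive. The intervention takes about 30 minutes. Women in conditions 1 to 5 complete four questionnaires, whereas "the control group receives this at three points in time". The questionnaire without a control counterpart is T1, completed between the standard session and the intervention. After the intervention, "all participants receive a BRISC brochure in which risks are presented corresponding to the format" of the intervention received. The limitations part of the Discussion notes that the additional consultations are given by members of the research team.

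The Statistical analyses section compares outcomes "between the five different intervention groups and the control group".

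**The concern.** To tell two effects apart, a design needs at least one condition in which one is present and the other absent. Here repetition and structure always occur together. The article nevertheless attributes structure to condition 5 and repetition to the contrast of 5 with 6, as if that contrast differed in repetition alone.

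The Hawthorne statement has a related weakness. Condition 6 has no additional contact and one questionnaire fewer, so a difference between condition 5 and condition 6 still contains any effect of attention and of being questioned again.

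The interpretation is at stake. A report following the article could credit repetition with an effect that came from structure, contact, written material or re-testing. A difference between a format condition and condition 6 likewise carries the whole package as well as the format. The Sample size and power section refers to the intervention group against the control group, and the Intervention section defines the control group as condition 6, so such a comparison is likely to be reported.

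**Working it through.** The article gives no figure for this point. The check is which effects the six condition means can identify.

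**Components, from the Intervention and Procedure sections and the Discussion**

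| Component | Condition 5 | Condition 6 |
|---|---|---|
| R: risk information repeated | yes | no |
| S: structured presentation | yes | no |
| C: about 30 minutes with a research-team risk counsellor | yes | no |
| B: brochure in the intervention format | yes | no (inferred) |
| Q: T1 questionnaire | yes | no |

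Conditions 1 to 4 share all five components with condition 5. They add natural frequencies (F) and, depending on the condition, the graph (G), age-related risk (A) and the interaction of the two (GA).

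**Condition means.** Effects are taken as additive, which is the most favourable case for separating them.

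- m6 = μ
- m5 = μ + R + S + C + B + Q
- m1 = m5 + F
- m2 = m5 + F + G
- m3 = m5 + F + A
- m4 = m5 + F + G + A + GA

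**What can be estimated**

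- m5 − m6 = R + S + C + B + Q. Only this sum is available.
- There are 10 parameters (1 intercept, 5 package components, 4 format terms) and 6 means. The design matrix has rank 6. A rank check shows that R, S, R − S, C, B and Q are each not estimable.
- With only R and S as differences there are 7 parameters and still 6 means. R and S remain inseparable. The result does not depend on the number of components counted.
- m1 − m5 = F; m2 − m1 = G; m3 − m1 = A; (m4 − m3) − (m2 − m1) = GA. All format terms are estimable, and the package cancels from each.
- m1 − m6 = F + (R + S + C + B + Q). Any format condition compared with condition 6 gives format plus package.

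Sample size plays no part: more women sharpen the estimate of the sum but do not divide it.

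**Hawthorne effects.** Women in condition 6 are invited, give consent and are measured at baseline, 2 weeks and 6 months. Change due to being in a study is therefore present in both conditions and largely cancels. C and Q are not matched and do not cancel. Between conditions 1 to 4 and condition 5 both are matched.

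**The case against.** Four points can be made for the article.

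**The Discussion sentence may mean less than it says.** It goes on to a second distinction, between formats given in a structured way. Read loosely, it sets repetition and structure together (5 versus 6) against format (1 to 4 versus 5), which the design can do. That reading is possible. But the sentence names repetition and structure as two things to be distinguished, and the Intervention section gives each its own control. If the looser meaning is intended, the text should say so.

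**The format comparisons are sound.** A reader might infer that the trial will pass off the consultation package as a format effect. The documents do not support that. The first three research questions concern adding the graph, adding age-related risk, and combining them. The Intervention section says condition 5 is there so that formats can be compared. The Statistical analyses section covers all six groups and does not restrict format conclusions to contrasts with condition 6, and neither does the sample size statement. This objection stands. What remains is that the analysis section could be explicit.

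**Condition 6 is of some use against Hawthorne effects.** A reader might infer that it offers no control at all. That too goes beyond the documents, because it shares enrolment and most of the measurement. Only extra attention and the extra questionnaire are left uncontrolled.

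**The list of differences can be disputed.** The brochure sentence refers to all participants. Excluding condition 6 is an inference from the sentence's link to an intervention that condition 6 does not receive. Contact with the risk counsellor is also the means by which the information is repeated. Both points are fair, but two components that always occur together are enough.

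**Conclusion.** The concern holds for the claim about repetition and structure. The design lacks a property that the Intervention section and the Discussion assign to it: 5 versus 6 estimates the combined effect of the additional consultation and nothing finer. The Hawthorne statement "and will control for Hawthorne effects" is true only for the effect of being enrolled and measured.

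No numerical size can be given. The documents hold no component effects, and if components had opposite signs the share due to repetition could be negative or exceed the whole, so even a range would be misleading.

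The conclusion rests on the article's description of what each condition receives. The brochure exclusion is an inference, but nothing depends on it. The consequence is limited: none of the four research questions asks about repetition or structure as such, and contrasts within conditions 1 to 5 are untouched. It still changes what the trial may conclude from its comparisons with usual care.

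**What to change.** - **Intervention and Discussion:** describe 5 versus 6 as the effect of the whole additional consultation (repetition, structure, contact, T1 questionnaire and, if condition 6 does not receive it, the brochure). Withdraw the claim that repetition and structure can be distinguished.
- **Intervention, Hawthorne statement:** limit it to the effect of being enrolled and measured, and name condition 5 as the attention-matched control for conditions 1 to 4.
- **Statistical analyses:** state that conclusions about formats rest on contrasts within conditions 1 to 5 (each format versus 5; 2 versus 1, 4 versus 3, 3 versus 1, 4 versus 2), and that any contrast with condition 6 is format plus consultation package.
- **Procedure:** say whether condition 6 receives a brochure.

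These changes cost wording only, and the claim for 5 versus 6 becomes more modest. Giving the control group a T1 questionnaire after the standard session is optional, at about 75 questionnaires (450/6, assuming equal groups). It would equalise the number of measurements but would not separate repetition from structure.

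### Table 2 is an incomplete 3×5 cyclic layout, so the schedule and a pooled control group can reduce but not eliminate time bias unless round is modelled

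*Protocol article*

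**What the plan says.** The Randomisation section states: "The inclusion period is divided into condition rounds using a Latin Square design". On timing it adds: "Every round takes 5 months and switches when a total of n = 75 is reached". On purpose it says: "The ranking order of conditions (1–5) is varied to correct for learning effect by the risk counsellors". Table 2 then gives the orders:

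- "Centre A 1 2 3 4 5"
- "Centre B 2 3 4 5 1"
- "Centre C 5 1 2 3 4"

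Condition 6, usual care without a risk consultation, is recruited alongside every round. The Discussion says that the design and this control group "both serve to eliminate bias due to time". The Procedure section assigns one risk counsellor to each centre. The Statistical analyses section compares pre-test (T0/T1) with post-test measures across the six groups and names personal variables as covariates.

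**The concern.** A complete Latin square for five conditions needs five rows, so that every condition occurs once in every period. Three centres supply only three rows. Time and condition are therefore partly confounded, and the layout alone does not have the property that the Discussion credits to it.

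Conditions 1–4 form the 2×2 comparison behind research questions 1 to 3. If women's response to the consultation changes over the 25 months of Table 2, or if the counsellors deliver it better with practice, part of that change would appear as a format effect. With one counsellor per centre, round number also measures that counsellor's experience. The exposed contrasts are the age-related effect (question 2) and the interaction (question 3). The graphical effect (question 1) is nearly balanced.

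**Working it through.** **Stated figure.** The article gives no mean round to reproduce. Its sample size is consistent: 6 × 60 = 360, and 360/(1 − 0.20) = 450.

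**Inputs.** The orders come from Table 2, and 60 analysed women per condition from Sample size and power. I assume equal cells: 60/3 = 20 women per centre and round in the active conditions, and 60/15 = 4 controls per centre and round.

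**Step 1: rounds of each condition.**

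| Condition | Centres A, B, C | Mean round | Never in rounds |
|---|---|---|---|
| 1 | 1, 5, 2 | 2.67 | 3, 4 |
| 2 | 2, 1, 3 | 2.00 | 4, 5 |
| 3 | 3, 2, 4 | 3.00 | 1, 5 |
| 4 | 4, 3, 5 | 4.00 | 1, 2 |
| 5 | 5, 4, 1 | 3.33 | 2, 3 |

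Condition 6, if recruited evenly, has mean round 3.0.

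**Step 2: shift of each contrast under a linear drift d per round, with no round term.**

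- 4 versus 2: 4.00 − 2.00 = 2.0d
- Age-related effect: (3.00 + 4.00)/2 − (2.67 + 2.00)/2 = 1.17d
- Interaction: (4.00 − 3.00) − (2.00 − 2.67) = 1.67d
- Graphical effect: (2.00 + 4.00)/2 − (2.67 + 3.00)/2 = 0.17d
- 4 versus control: 4.00 − 3.00 = +1.0d; 2 versus control: 2.00 − 3.00 = −1.0d

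Each condition occurs once in each centre, so a centre term alone changes none of these.

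**Step 3: false-positive rates.** The document gives no drift, so d is an assumption, shown over a range. The rate is P(|Z| > 1.96) with Z normal, variance 1 and mean equal to shift/SE. In SD units, the SE is √(2/60) = 0.183 for 4 versus 2 and √(1/60) = 0.129 for the age-related effect. For example, at d = 0.1 the means are 0.200/0.183 = 1.10 and 0.117/0.129 = 0.90.

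| Assumed d (SD per round) | 4 versus 2 | Age-related effect |
|---|---|---|
| 0.02 | 5.6% | 5.4% |
| 0.05 | 8.5% | 7.4% |
| 0.10 | 19.5% | 14.8% |

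**Step 4: with round and centre terms, conditions 1–5 only.** The model has full rank (11 columns, 15 cells). A drift common to the centres then contributes 0 to every contrast. The ratio of adjusted to unadjusted variance is 1.06 for the graphical effect, 1.15 for 2 versus 1, 1.23 for the interaction, 1.31 for 4 versus 2 and 1.39 for the age-related effect.

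**Step 5: what happens if the controls share the round effects.** Condition 6 has no risk consultation, so it carries no counsellor learning. If the drift occurs only in the active conditions and the 4 controls per cell help to estimate common round effects, some bias remains: 0.43d for 4 versus 2, 0.26d for the age-related effect and 0.35d for the interaction.

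**The case against.** The strongest reply is that the analysis section is a short summary in an article, and that round and centre may well be in a fuller plan. That stands. A reader might infer that the trial will be analysed without a round term, but the article does not say so, and the absence of a model specification is not the point here. What remains is that the article attributes removal of time bias to the schedule and the control group, and these cannot deliver it by themselves.

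Three other strong readings also go too far.

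- A reader might take the article to claim that learning bias is eliminated. It claims elimination for time only; for learning it says that varying the order is meant to correct for it.
- A reader might conclude from the cyclic shifts that the order is not varied. Positions are varied: condition 1 falls in rounds 1, 5 and 2. What the shifts fix is which condition precedes which. Since each woman receives a single condition, that matters little.
- A reader might suppose that any drift passes into the format contrasts. T1 is taken after standard counselling and before the consultation. Drift in case mix or usual counselling that moves T1 and T2 equally therefore cancels in the change between them. Drift in the change itself, or in delivery of the consultation, does not cancel.

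It is also fair that the counsellors are specifically trained, so learning may be small, and that 0.1 SD per round is only the top of an assumed range.

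**Conclusion.** The concern holds as a correction to a stated property of the design. The imbalance follows exactly from Table 2: up to two rounds between conditions 4 and 2, 1.17 rounds for the age-related effect, 1.67 for the interaction and a negligible 0.17 for the graphical effect. Its consequence depends on a drift that the document does not give. Under linear drift common to all centres, the effect on error rates runs from trivial at 0.02 SD per round to serious at 0.1 SD. This is not evidence that the trial's results will be biased. The design is connected, so an ordinary model with round terms recovers every format contrast, at a price in precision.

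**What to change.** 1. Enter round, with centre, as fixed effects in every model that compares conditions. Round does the work; centre is already balanced if cells are equal.
2. For the format contrasts among conditions 1–5, estimate the round effects within those conditions, for the reason given in step 5 of the working.
3. State that contrasts with condition 6 can be adjusted for calendar trend but not for counsellor learning.
4. Describe Table 2 as an incomplete cyclic design of three centres by five rounds. In the Discussion, replace *eliminate* with *reduce*.

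The cost is wording plus the variance increases in step 4 of the working, from about 6% (graphical) to 39% (age-related). The adjustment removes only drift common to the centres; learning that differs between the three counsellors would remain.

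Reordering Centre C to 5, 4, 1, 3, 2, if its later rounds are still open, is optional. It brings the mean rounds to 3.00, 2.67, 3.00, 3.00 and 3.33 and cuts the age-related imbalance from 1.17 to 0.17 rounds. It is not the main remedy, because it raises the adjusted variance of the age-related effect (0.0251 against 0.0218, in units of the outcome variance, in the model with controls).
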